### Lost-to-follow-up and missing data

If a participant in the ancillary MRI study has an ischemic stroke or recurrent ICH before the end of the 2-year follow-up period and a clinical MRI is obtained for stroke assessment at one of the participating sites, this MRI may serve as the end-of-study MRI if it complies with the study imaging protocol and the subject is unable to return for the 24-month follow-up MRI. If the clinical MRI indicates the presence of new markers, this indicator will be carried forward to the end-of-study timepoint. The data will be considered missing if the MRI does not show new markers and is performed more than 3 months prior to the participant’s anticipated end-of-study visit. Missing outcome data related to the incidence of MRI markers will be handled in the analysis via multiple imputation.

Multiple imputation is generally considered the least biased imputation method, since it incorporates uncertainty associated with the imputed value into the analysis. Briefly, logistic regression is used to derive a distribution for the primary outcome, using the primary analysis covariates (treatment, statin dose and indication, current use or intent-to-use oral anticoagulants and/or antiplatelets post-ICH, and severity of enrolling ICH) plus additional clinically relevant baseline variables. A random sample from the resulting distribution is used to impute values. Multiple sample data sets with complete primary outcome data are generated; each imputed data set will be analyzed according to the specified primary analysis, and the results from the multiple imputed data sets are combined to obtain a single set of parameter estimates. The multiple imputation method assumes missing at random (MAR) which means that the probability of missing outcome data can depend on the observed values of the individual but not on the missing values of the individual.

## Discussion

Patients with spontaneous lobar ICH often have varying degrees of underlying CSVD on MRI, and the effects of long-term statin therapy on the burden of CSVD have yet to be defined. Statin therapy could interact with CSVD in various fashions. On one hand, statin use in ICH patients may be independently associated with the presence and number of CMBs, particularly in lobar locations [6, 8]. Statins possess plausible biological mechanisms by which they might increase the propensity for intracranial bleeding independent of lipid lowering by inhibiting platelets, decreasing thrombus formation, and enhancing fibrinolysis [24–26]. These properties of statins could accelerate the incidence/accrual of hemorrhagic markers of CSVD such as CMBs and cSS [7]. On the other hand, the putative anti-inflammatory, antiplatelet, endothelial stabilization, and cerebral vasoreactivity-enhancing properties of statins could reduce the accrual of covert infarcts and WMH over time [8, 27–31] Statins might additionally mitigate the contribution of concurrent atherothrombotic vascular disease to the accrual of covert infarcts and WMH [27–29, 31].

The SATURN trial is limiting eligibility to lobar ICH as a pragmatic means of deriving a CAA-enriched population. However, not all spontaneous lobar ICH are due to CAA in older populations, with a proportion resulting from underlying hypertensive arteriopathy [32]. The use of MRI would further help to improve the diagnosis of CAA through the use of the clinico-radiographic Boston Criteria. Moreover, even within CAA cohorts, response to stroke preventive treatments has been shown to differ depending on the severity of underlying disease manifested by MRI biomarkers [33]. MRI would allow assessment of treatment interactions between baseline MRI phenotypes suggestive of advanced CAA (which might be at greatest risk for increased recurrent ICH with continued statin therapy) and statin continuation vs. discontinuation. The potential to use MRI markers, such as CMBs and cSS, to identify patients who benefit or are harmed from long-term statin therapy could facilitate individualized decision-making and risk stratification and would be an important and novel contribution to the field which could have important cost- and resource-saving implications. In practice, the results of SATURN MRI will be interpreted in concert with those of the main SATURN trial. An increased risk of ICH recurrence with statin continuation in the SATURN main trial and as well an increased risk of ICH recurrence in patients with CMBs/cSS on baseline MRI in SATURN MRI would indicate higher absolute risks of ICH recurrence and lower numbers needed to harm in patients with CMBs/cSS. Conversely, if SATURN main results do not show an increased risk of ICH recurrence with statin continuation, but SATURN MRI shows increased risk in patients with CMBs/cSS, the results can similarly lead to individualization of treatment decisions according to MRI phenotypes. However, if both SATURN and SATURN MRI do not show increased risk of ICH recurrence with statin continuation, this would provide reassurance supporting the safety of statins among the highest risk subgroups of lobar ICH patients and could lead to avoidance of unnecessary neuroimaging in clinical practice and hence save costs.

Furthermore, observations from SATURN-MRI could lead to novel hypotheses for further research elucidating the pathogenesis of CSVD implicated in lobar ICH and ultimately lead to novel therapeutic targets aimed at mitigating the progression of microvascular cerebral injury and ensuing disability. The progression of markers of CSVD may be influenced by other variables such as adequacy of blood pressure (BP) control and use of anti-thrombotic drugs [30, 34]. The SATURN trial already adjusts for the use/intent-to-use of anti-thrombotic drugs in its randomization scheme. Participants are also asked to check and report their BP at follow-up assessments and are reminded at all points of contact of the importance of maintaining BP ≤ 130/80 mmHg. To address this, we also plan to perform post hoc correlation-type analyses to examine the impact of post-randomization variability in the use of anti-thrombotic drugs and adequacy of BP control on imaging outcomes.

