### Statistical considerations

#### Sample size calculations

The target sample size is 894, based on the following observations/assumptions. We previously reported that 57% of statin-treated patients admitted with acute lobar ICH had CMBs on MRI [6]. Although the estimated incidence rate of new CMBs per year in patients with lobar ICH on/off statins is unknown, the annual incidence rate in mixed stroke cohorts varies from 3 to 7% per year (average ~ 5% per year) [18–21]. In a cohort of 118 patients with probable CAA, 8.5% showed new CMBs without cSS progression, 18.6% showed cSS progression without new CMBs, and 9.3% showed new CMBs and cSS progression, for a total of 36.4% with progression of either CMBs and/or cSS over the 2.2 years of follow-up, or approximately 19% per year [18]. These data likely overestimate the incidence rate expected in SATURN-MRI because approximately 33% of SATURN patients are expected to have probable CAA, and another 40% possible CAA. Therefore, we opted to select a more conservative new CMB and/or cSS rate of 6% per year, for a total of 12% over 24 months in patients discontinuing statins. We postulated that statin therapy will increase the risk of new CMB and/or cSS at a rate that is similar to that reported for ICH in the SPARCL trial (HR 1.68, or absolute increase of 8% over 24 months). Based on these assumptions, a two-group comparison of independent proportions with 652 subjects will yield 80% power to detect an absolute increase of 8 percentage points associated with the continuation of statin therapy in SATURN. This sample size was further inflated to account for loss-to-follow-up (LTFU), withdrawal-of-consent, and death during the 2-year follow-up period of approximately 15%, as observed in other MRI sub-studies, such as NAVIGATE-ESUS [22] and PURE [23].

The sample size calculation assumes 1:1 statin continuation:discontinuation among subjects enrolled in the ancillary SATURN-MRI study, but this balance is not guaranteed. However, the power is maintained above 75% for allocation ratios in the interval between 0.6 (discontinuation arm 62.5% of the total sample) and 2.5 (discontinuation arm 28.6% of the total sample).

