#### Analyses related to the secondary aims

In order to explore whether the presence and burden (number) of CMBs on baseline MRI can be used as an imaging marker to stratify the risk/benefit of statin therapy, a proportional hazards model will be used to relate the time to symptomatic ICH recurrence to treatment assignment, the presence and burden of CMBs/cSS, and the corresponding interaction. The interaction term will be used to evaluate the heterogeneity of the treatment effect according to presence/burden, and the corresponding treatment effects and 95% confidence intervals will be constructed. The effects of statin continuation on the incidence of new ischemic MRI markers (WMH and covert infarcts) on end-study MRI will be evaluated via logistic regression model relating the presence of new markers to treatment assignment. Heterogeneity of the treatment effect across racial/ethnic subgroups will be explored by extending the proportional hazards model to include main effects for sex and racial/ethnic subgroups and their corresponding interactions with treatment and presence/number of new lesions.

The association between the incidence of new MRI markers on end-study MRI and deterioration of cognitive function, quantified by T-MoCA, and functional outcome, quantified by mRS, will be evaluated. As in the parent trial, the T-MoCA will be analyzed by considering cognitive decline (reduction of at least two points from the highest score to any subsequent assessment), as well as normal cognition (T-MoCA ≥ 20); the mRS will be dichotomized (0–3 vs 4–6). A generalized linear mixed effects model will be constructed for each outcome independently in order to relate outcome to treatment, time, and presence of new lesions; in addition to the adjustments for randomization covariates specified above, the models will include an indicator for baseline cognitive decline/dementia derived from the subject’s medical history.

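### The Discussion counts no demonstrated increase in recurrent ICH as reassurance for CMB/cSS-positive patients without requiring any precision, although SATURN-MRI is sized only for new CMBs/cSS

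*Protocol article*

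**What the plan says.** The Discussion sets out how SATURN-MRI will be read together with the parent trial. One of its scenarios is a null result in both: "if both SATURN and SATURN MRI do not show increased risk of ICH recurrence with statin continuation, this would provide reassurance" about statin safety in the lobar ICH patients at highest risk. It adds that this could spare patients unneeded imaging. From the surrounding text, these are the patients with CMBs and/or cSS at baseline. The sentence sets no condition on how precise the null result must be.

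The section on secondary aims plans a proportional hazards model for time to symptomatic ICH recurrence, with treatment, baseline CMBs/cSS and their interaction. It states that "The interaction term will be used to evaluate the heterogeneity of the treatment effect according to presence/burden", and it promises treatment effects with 95% confidence intervals. The aim is framed as exploratory.

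The sample size section concerns a different outcome, new CMBs and/or cSS. "The target sample size is 894", built on the statement that "652 subjects will yield 80% power to detect an absolute increase of 8 percentage points". The control rate is 6% per year, "for a total of 12% over 24 months in patients discontinuing statins". The effect comes from an earlier statin trial's ICH result ("HR 1.68, or absolute increase of 8% over 24 months") and is applied to imaging lesions: "We postulated that statin therapy will increase the risk of new CMB and/or cSS at a rate that is similar to that reported for ICH". The article gives no rate, event count or power for recurrent ICH, overall or by marker status.

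**The concern.** Failing to show an increase is informative about safety only when the estimate is precise enough to rule out an increase that matters. The Discussion passes from the first to the second without asking for that precision. It does so for the subgroup that the article itself regards as possibly most exposed to harm, and on an outcome for which the study was not sized.

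Read as written, a wide confidence interval around a null estimate in marker-positive patients would satisfy the sentence as well as a narrow one. At stake is a statement about safety in those patients, and a suggestion that imaging may be unnecessary, both resting on absence of evidence.

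**Working it through.** **Inputs from the article.** Target 894; 652 evaluable; 12% versus 20% for new lesions; 80% power; 1:1 allocation; HR 1.68; 57% of statin-treated lobar ICH patients with CMBs; 95% confidence intervals for the subgroup effects; 2-year follow-up.

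**Assumptions.** Two-sided alpha of 0.05 (not stated, but consistent with 95% intervals). The marker-positive subgroup is 0.57 × 894 = 510 patients. The two-year recurrent ICH risk is not given, so a range is shown.

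**1. The plan's own figure.** For two proportions with unpooled variance:

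n per arm = (1.960 + 0.842)² × (0.12 × 0.88 + 0.20 × 0.80) / 0.08² = 325.7, so 326 per arm and 652 in total.

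The stated 652 is reproduced. It answers the question on new lesions and carries no information on power for recurrent ICH.

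**2. Precision for recurrent ICH in the subgroup.** With 1:1 allocation and d events, SE(log HR) = 2/√d, and ln 1.68 = 0.519.

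- Events at which an observed HR of 1 has an upper 95% limit of exactly 1.68: d = (2 × 1.96 / 0.519)² = 57. In 510 patients, 57/510 = 11.2% two-year recurrence.
- Events for 80% probability that the upper limit falls below 1.68 when the true HR is 1: d = 4 × (1.960 + 0.842)² / 0.519² = 117. In 510 patients, 117/510 = 22.9%.

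**3. Results by assumed recurrence risk (510 patients).**

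| Two-year risk | Events | Upper 95% limit if observed HR = 1 | P(exclude 1.68), true HR 1 | P(non-significant), true HR 1.68 |
|---|---|---|---|---|
| 3% | 15 | 2.73 | 17% | 83% |
| 5% | 25 | 2.17 | 26% | 74% |
| 10% | 51 | 1.73 | 46% | 54% |
| 15% | 76 | 1.57 | 62% | 38% |
| 20% | 102 | 1.47 | 74% | 26% |
| 25% | 127 | 1.42 | 83% | 17% |

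Example at 10%: SE = 2/√51 = 0.280; upper limit = exp(1.96 × 0.280) = 1.73; power for HR 1.68 = Φ(0.519/0.280 − 1.96) = 46%, so 54% of such results would be non-significant.

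**4. Sensitivity to subgroup size.** The 57% counts CMBs only, so a subgroup defined by CMBs and/or cSS would be at least as large. The article's CAA shares (33% probable, a further 40% possible) are used only to vary the size.

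| Subgroup | Risk at which an observed HR of 1 just reaches 1.68 | Risk for 80% probability of excluding 1.68 |
|---|---|---|
| 295 (33% of 894) | 19.3% | 39.7% |
| 372 (57% of 652) | 15.3% | 31.5% |
| 510 (57% of 894) | 11.2% | 22.9% |
| 653 (73% of 894) | 8.7% | 17.9% |

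**The case against.** The strongest reply is that this is conditional Discussion wording and not a decision rule. It names no alpha, test or threshold, and non-significance is only one reading of not showing an increase. It also requires a null result in both studies. The parent trial's main question is recurrent ICH, and its design is described elsewhere, so how much its result would add cannot be judged here. All of this stands and limits the point to interpretation. It does not supply the missing condition: a null parent result averages over marker-negative patients and does not by itself settle the marker-positive ones.

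Three stronger readings are tempting, and the documents do not support them.

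- *The subgroup cannot exclude 1.68.* This is too categorical. It depends on a recurrence risk the article does not give; above about 11% in 510 patients, an observed HR of 1 would exclude it.
- *Marker-specific harm will be claimed from a subgroup result without an interaction test.* The Discussion scenario of a null parent trial with increased risk in marker-positive patients might suggest this. But the section on secondary aims assigns heterogeneity to the interaction term, and the Discussion itself speaks of assessing treatment interactions.
- *HR 1.68 is the plan's safety margin.* It was postulated for new lesions as a harm to detect. It is used here only as a yardstick, and the article offers no basis for any recurrent ICH margin.

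Nor is it a defect that a condensed article omits the detectable interaction for an exploratory aim, or that the study is sized on its primary outcome.

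**Conclusion.** The point holds as one about interpretation. The Discussion attaches reassurance in the highest-risk patients to a null result without asking how precise that result is, and nothing in the sample size section shows that it would be precise.

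Taking 510 marker-positive patients, 1:1 allocation and two-sided 5% tests, a true HR of 1.68 would be missed more often than not at two-year recurrence of 10% or less. Below about 23%, the chance of excluding 1.68 when statins have no effect is under 80%. A larger marker-positive share lowers these thresholds and a smaller one raises them. Since the recurrence risk is an assumption throughout, the figures show how precision varies and do not predict the result. The primary analysis, the data to be collected and the planned models are unaffected.

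**What to change.** Reword the Discussion so that reassurance in marker-positive patients is claimed only if the upper 95% confidence limit of the subgroup HR for recurrent ICH lies below a margin that the sponsor fixes and justifies before results are known. Otherwise the result is to be called inconclusive. The interval is already planned in the section on secondary aims. State in the same place that marker-specific harm will be judged on the planned interaction estimate with its confidence interval, as an exploratory finding.

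The cost is a few sentences and one justified margin, with no new patients, data or analyses. The downside is that a null result may have to be reported as inconclusive.

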## Summary and conclusions

SATURN-MRI provides a unique opportunity to evaluate the effects of long-term statin therapy on the burden of CSVD. As an ancillary study of the SATURN trial [14], SATURN-MRI will allow us to efficiently examine the prognostic and pathophysiological characteristics of MRI biomarkers of CSVD within the scope of a large-scale, prospective, randomized, controlled trial. The results from SATURN-MRI will have direct clinical relevance and could lead to validation of MRI imaging markers as tools to assist with individualized decision-making regarding the safety of statin use/continuation in ICH patients and the mitigation of late-life cognitive and functional decline.

## Data Availability

The final results of this study will be made available on the clinicaltrials.gov (NCT03936361), and data generated will be publicly available through the NINDS Archived Clinical Research Dataset. The study will follow NIH policies on data sharing (as described at http://grants2.nih.gov/grants/policy/data_sharing/data_sharing_guidance.htm) and any updates thereto. A complete de-identified dataset will be made available via the NIH Archived Clinical Research Datasets (https://www.ninds.nih.gov/Current-Research/Research-Funded-NINDS/Clinical-Research/Archived-Clinical-Research-Datasets) within one year of manuscript publication. The dataset will be made available for limited use to researchers whose proposed use of the data is approved by the NIH/NINDS in accordance with the terms and conditions of the NINDS data request form (https://www.ninds.nih.gov/sites/default/files/NINDS_Data_Request_Form_508C.pdf).

## Abbreviations

ICH: Intracerebral hemorrhage
CSVD: Cerebral small vessel disease
MACCE: Major adverse cardio- and cerebrovascular events
MRI: Magnetic resonance imaging
CAA: Cerebral amyloid angiopathy
CMB: Cerebral microbleed
cSS: Cortical superficial siderosis
WMH: White matter hyperintensities
PVS: Perivascular spaces
RCT: Randomized controlled trial
GRE: Gradient-echo
SWI: Susceptibility-weighted image
SWAN: Susceptibility-weighted angiography
UC: University of Cincinnati
IRB: Internal Review Board
NINDS: National Institute of Neurological Disorders and Stroke
NIH: National Institute of health
